## 5. Selection of subjects

### Population

Patients of both sexes, from 18 to 60 years-old with diagnosis of CHB will constitute the study population. These patients must, at least, be free of any specific treatment for CHB in the past 6 months before the inclusion in the study.

### 5.2 Diagnostic Criteria

The diagnosis will be established by

- HBV surface antigen (HBsAg) in serum for more than 6 months
- Presence of HVB DNA in serum with a detectable viral load according to quantitative PCR analysis

- One abnormal ALT value in the last year before immunization or history of chronic hepatitis verified by biopsy (Biopsy will not be a requisite, however, it should be stimulated for those requiring such procedure according to current clinical practice in Bangladesh)

### 5.3 Inclusion criteria

- HBsAg+ serology for more than 6 months before the beginning of the treatment.
- HBeAg (-) patients, with a) baseline HBV DNA  $\geq 10^3$  and b) raised serum ALT ( $> 1 \times \text{ULN}$ ) or significant hepatic necro-inflammation and or fibrosis (HAI-NI $\geq 4$  and/or HAI-F  $\geq 2$ ), or stiffness  $> 7.2$ .
- HBeAg (+) patients, with a) baseline HBV DNA  $\geq 10^4$  and b) and raised serum ALT ( $> 1.5 \text{ ULN}$ ) or significant hepatic necro-inflammation and or fibrosis (HAI-NI $\geq 4$  and/or HAI-F  $\geq 2$ ) stiffness  **$> 7.2$** .
- 18 to 60 years-old patients of both sexes.
- No specific hepatitis B treatment at least for 6 months previous to the inclusion
- Voluntary signed informed consent to participate in the trial

### 5.4 Exclusion criteria

- Condition of asymptomatic HBV carrier, cirrhotic or primary hepato-cellular carcinoma patients
- Positive serological markers for hepatitis C or hepatitis delta virus.
- Positive serological markers for HIV
- Previous specific anti-hepatitis treatment in the last 6 months.
- Critically ill patient, heart or renal failure, hypertension, hyperthyroidism, epilepsy, immunodeficiency diseases, malignancies or any non-controlled systemic disease.
- Pregnancy or nursing women. Women in fertile ages without any contraceptive methods.
- Known severe allergic conditions (degree III or IV asthma, urticaria, dermatitis, bronchitis, etc. or hypersensitivity to any of the ingredients present in the preparation such as thiomersal.
- Severe psychiatric dysfunction or another limitation that prevents the patient's consent.
- Autoimmune diseases (such as lupus, rheumatoid arthritis, multiple sclerosis, non controlled diabetes mellitus type 1)

- Other hepatic diseases of different etiology (such as alcoholism, auto immune hepatitis, toxic hepatitis, Wilson diseases, hemochromatosis)
- Treatment with immune suppressive disorder or administration of immune suppressive-immune modulator drugs (including steroids) during or in the 6 months previous to the study.
- Very high transaminase levels at the beginning of treatment (ALT over 500 U/L) suggesting a not stable disease with risk for patient's health or acute flares over 15 times the upper limit of normality.

### **5.5 Exit criteria or interruption of the treatment after inclusion**

- Voluntary abandonment of the patient.
- Appearance of any of the above-mentioned exclusion criteria.
- Patients with worsening of the liver pathology in comparison with baseline levels, according to the investigator's criteria.
- Severe adverse reactions according to WHO guidelines
- Feverish status (more than 37.8 °C) at the moment of vaccine administration or in the 24 hour before, or any suspected or confirmed infectious diseases that results in the suspension of three vaccine administrations during the course of the immunization schedule.
- Patient's death.

Patients, once included, will be considered in the analysis even if they interrupt the treatment. Therefore, no case report form will be eliminated.

## **6. Treatment**

### **Products to be used**

#### **General characteristics of the NASVAC TVC**

- NASVAC TVC composition and specifications are contained in the dossier provided with the present protocol. Briefly:

per 1 bb (500 mcL) NASVAC formulation contains:

| Component                                                                        | NASVAC TVC (per 0.5 mL)          |
|----------------------------------------------------------------------------------|----------------------------------|
| Recombinant HBsAg, produced in Pichia pastoris , immunopurified.          | 50 µg                            |
| Recombinant HBcAg, produced in E coli , purified over 95% of purity.      | 50 µg                            |
| Sodium chloride                                                                  | 4.0 mg                           |
| Dibasic sodium phosphate (anhydrous)                                             | 5,6 mg                           |
| Dehydrated monobasic sodium phosphate or Monohydrated monobasic sodium phosphate | 0.62 mg or 0.55 mg, respectively |
| Water for injection, up to                                                       | 0.5 mL                           |

### Treatment schedule

The NASVAC TVC will be administered **to SG1** during the first cycle in a final volume of 1.0 mL (100µg of HBsAg and 100µg of HBcAg) by intranasal route with 8 actuations of 125 µL until completing . The second cycle will continue the IN administration in the same dosis and frequency and simultaneously the same treatment will be administered by the SC route. The device to be used (Valois VP7D spray pump) will be actuated with five minutes intervals between actuations in the same nostril.

The pegylated IFN will be administered **to SG2** weekly by subcutaneous route in the established dose (180µg) .

### Rules for the use of concomitant treatments

- Any specific anti hepatitis treatment should be avoided, as well any other investigational drug.
- Other drugs that can affect the immune system should also be avoided (corticosteroids, immune-suppressors, immune-stimulants, cytokines, etc.).

### Measures to guarantee safety in the manipulation of the products

1. Experienced personnel will carry out the administration of the medications in the clinic.
2. NASVAC and IFN vials should be stored at 2 to 8 °C (domestic refrigerators) until use.
3. The access to all products will be limited and controlled by the principal investigator or the person designed by him.

4. The vials that are not used, as well as empty vials, should be returned to the sponsor.
5. The product should not be used for another purpose besides this clinical trial.

#### **Measures to promote and control that the instructions and prescribed rules are followed**

1. An included- and not included-patients register will be kept.
2. The sponsors will verify storage conditions and use of the products in the quality control visits by monitors or by any other persons officially designated by the sponsors.
3. The treatment will be controlled through a control card, where each administration will be registered.
4. The investigators will know the analysis certificate of the products in order to begin trial.
5. The investigators, properly trained for it, will carry out the whole treatment.
6. A physician that includes a case will continue his follow-up and will be responsible for the suitable control of the complementary tests.

## **7. Evaluation**

#### **Evaluation criteria regarding immunogenicity / efficacy**

##### **Main variable**

The main variable of efficacy is the HBV DNA viral load quantification in serum.

##### **Secondary variables**

Serological markers: HBeAg and anti-HBeAg, HBsAg and anti-HBsAg

Biochemical markers: liver transaminases (ALT and AST)

Other parameters regarding basic hematology and clinical biochemistry (bilirubin, alkaline phosphatase etc).

Histology: histological grade and stage

##### **Control variables**

- Age
- Sex

- Weight
- Body mass index
- Duration of the disease
- Initial viral load
- Smoking and other toxic habits

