Virological response was assayed after five and ten doses. The HBeAg negative group of patients behaved better in terms of HBV elimination by quantitative PCR (detection limit 250 copies/mL) compared to HBeAg positive group. From 13 HBeAg patients receiving five intranasal doses of NASVAC, six patients reduced the viral load to undetectable levels for 46% just after five intranasal doses. None of the six patients clearing the virus were over the ULN for ALT after the fifth or after dose number 10, even when four of them had a mild ALT flare during the first cycle of IN administrations, suggesting a quick immune response. The absence of ALT increase during treatment in two patients clearing the virus suggests that non-cytolytic mechanisms were also activated. For patients clearing the virus, ALT increases ranged between 1.5 and 3 times the ULN, such increases where in one or two consecutive determinations only, suggesting that the potentially curative effect of vaccination was associated at least to small and quick flares of ALT levels. Such increases were not clinically apparent as patients didn't report any adverse event during the course of the vaccination, and physicians didn't detect any related symptom, suggesting that the increases in ALT levels were not clinically apparent. Also, due to the temporal relation to the starting date of the protocol, it is reasonable to predict that it was associated to the vaccination. From literature is known that specific immune stimulation has been related to ALT increases and virological response in CHB patients.

In support of the results obtained after the end of treatment, the evaluation of the 6 month time follow up (time 12 months) evidenced a further decrease in the levels of HBV DNA to undetectable levels in 50% of total patients, being outstanding the behavior of HBeAg negative patients that reduced the viral load in 8 of 13 patients. HBeAg positive patients also evidenced strong reductions in viral load however the reduction to undetectable was reduced compared to HBeAg negative patients, which is understandable based in the fact that the baseline viral load values were much higher for HBeAg positive patients. For both groups ALT values evidenced a generalized normalization reaching 100% at month 9 and 95% at month 12..

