### **Design of the trial**

The population sample to be tested will be of 160 CHB patients, with variable serum transaminase levels, without treatment for at least 6 months, selected according to inclusion and exclusion criteria and allocated in two study groups (SG). The first study group, SG1 will include 80 CHB patients (HBeAg (+) and HBeAg (-)) that will be treated with 1 mL NASVAC (100 mcg per antigen, per dose per patient), administered in two cycles of inoculations, the first one by the intranasal route with five intranasal inoculations every 14 days each. During the second cycle patients will receive the same dosis (100 mcg per antigen) by the intranasal route and additionally the same dosis by the SC route,

The SG2 will be treated with Alpha-Interferon at standard dosis (weekly injection by SC route).

The treatment is discontinued for all patients of SG1 after completion of both cycles. The evaluation will continue during one year, but an interim report will be released after 5 and 10 administrations.

During the whole treatment period up to one year from the beginning of treatment, the systematic assessment of patients is launched to determine to what extent the treatment has driven them to generate the capacity to control the HBV load. This information is included in Figure 1.

[figure not shown]

**Figure 1.** General Algorithm of the trial

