### **Serology: Response:**

**HBeAg: Negativity:** disappearance from serum

**Seroconversion:** disappearance of HBeAg from serum and appearance of HBeAb.

**HBsAg: Negativity:** disappearance from serum

**Seroconversion:** Appearance of HBsAb in serum.

Both groups will be compared according to the categories defined above by the chi-square test or odds ratio calculation. A logistic regression will be also performed for a multivariate analysis of the influence of the different control variables that result significant in the previous univariate analysis. A signification level of  $p = 0.1$  will be considered. The potency will be of 80%.

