## **Evaluation of the biochemical status**

### **Transaminases: Response**

#### **ALT / AST:**

**Sustained normalization** (reduction to values under 40 IU during a period of three months time) in at least 20% compared to the initial number of patients with altered (more than 40 IU) at the beginning of treatment.

**Normalization:** Reduction to values under 40 IU after one year.

It will be studied for Interim analysis different periods of time and compared to baseline level as described in Interim analysis: after five dosis, after ten dosis, after 24 weeks (6 months) or after 56 weeks (one year)..

The ALT and AST values in serum will be compared between groups and within each group, as quantitative variables, by Student's t or the Mann-Whitney's U test, depending on the normality or not of their distributions. Paired analysis will be also performed within each group to know whether a significant change has occurred in these patients.

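### Baseline ALT and baseline HBeAg status are missing from the control variables, and the one multivariable efficacy model screens its covariates, so no analysis described in the protocol adjusts the HBV DNA comparison for either factor

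*Protocol*

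**What the plan says.** **Control list.** Protocol section 7, Control variables, names age, sex, weight, body mass index, duration of disease, "Initial viral load", and smoking and other toxic habits. ALT appears in the same section only as an outcome, under Secondary variables ("Biochemical markers: liver transaminases (ALT and AST"). HBeAg is likewise listed there only as a serological outcome.

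**Entry.** Section 4, Design of the trial, recruits patients "with variable serum transaminase levels". Section 5.3 sets separate HBV DNA and ALT limits for HBeAg-negative patients (ALT above 1 × ULN) and HBeAg-positive patients (above 1.5 × ULN). Raised ALT can be replaced by other findings ("or significant hepatic necro-inflammation and or fibrosis", or liver stiffness). Section 5.4 sets the upper end: "Very high transaminase levels at the beginning of treatment (ALT over 500 U/L".

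**Allocation.** Section 4 describes an open trial with patients allocated to two groups. It mentions neither randomisation nor stratification.

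**Model.** In section 10, after the serology definitions, a logistic regression is planned to examine "the influence of the different control variables that result significant in the previous univariate analysis". The only other logistic regression in section 10 concerns adverse events and uses the same control variables.

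**Criterion.** The hypothesis and the interim success rule in section 10 both turn on a 20-point difference in the percentage with undetectable HBV DNA.

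**The concern.** Two baseline features that decide who enters the trial, and at which limits, are not candidates for adjustment of the main comparison. If either predicts viral response and differs between arms, the HBV DNA difference moves towards or away from the 20-point criterion for a reason unrelated to treatment. Where allocation is not described as random, such an imbalance need not stay within what chance produces.

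The screening rule adds to this. A listed covariate stays in the model only if it is significant on its own, so even initial viral load may drop out. The position of the regression sentence, after the serology definitions, also leaves open whether it applies to HBV DNA at all.

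**Working it through.** The plan gives no figure for this point, so there is none to reproduce. The check is of the text first, then of the possible size.

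**1. Is either factor a candidate covariate?** The seven listed variables contain neither. The efficacy regression takes its candidates from that list. The factorial and cluster analyses in section 10 are exploratory and do not adjust the treatment comparison. So, as described, neither factor is adjusted for.

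**2. How wide is entry ALT?** The reference limit in the determinations table is 42 U/L; the ALT response definition uses 40 IU. 500/42 = 11.9 and 500/40 = 12.5. Entry therefore spans normal ALT to about 12 times the limit. The ALT response is counted "compared to the initial number of patients with altered (more than 40 IU" at the start, so the protocol itself expects a mixed population.

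**3. What does the protocol say about prognosis?**
- *HBeAg status.* Section 2.7 reports better HBV elimination in HBeAg-negative patients, with 8 of 13 undetectable at month 12, against 50% of all patients. If that 50% refers to all 20 patients, 10 − 8 = 2 of 7 HBeAg-positive patients were undetectable. That gives 61.5% against 28.6%, a gap of 33 points on very small numbers.
- *ALT.* Section 2.7 links viral response to the ALT peak after therapy starts and says that "specific immune stimulation has been related to ALT increases and virological response in CHB patients". These are on-treatment changes. No response rate by baseline ALT is given.

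**4. Possible shift from baseline ALT (assumed strength).** Take log ALT in SD units as a standard normal covariate X, with log odds ratio b = ln(1.3), ln(1.5) or ln(2.0). Choose the intercept a so that the mean of 1/(1 + exp(−(a + bX))) equals a response rate of 30, 40 or 50%. Then move X by d SD and take the change in the mean. The ranges below are over the three response rates.

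| Odds ratio per SD | d = 0.3 SD | d = 0.5 SD |
|---|---|---|
| 1.3 | 1.7–1.9 points | 2.8–3.2 points |
| 1.5 | 2.5–2.9 | 4.3–4.9 |
| 2.0 | 4.1–4.7 | 7.0–7.8 |

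**5. How large is chance imbalance?** The standard error of a difference in means, in SD units, is √(2/n). Section 4 gives 80 per arm (160 in total): √(2/80) = 0.158, and 1.96 × 0.158 = 0.31 SD. The sample-size paragraph gives 60 per group: √(2/60) = 0.183, and 1.96 × 0.183 = 0.36 SD. So 0.3 SD is about the 95% limit of chance. At 80 per arm, 0.5/0.158 = 3.2 standard errors, so the last column applies only if allocation is not random.

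**6. Possible shift from HBeAg status (illustration).** Assume the earlier study's HBeAg-positive share, 7/20 = 35%, and the 33-point gap from step 3. With 80 per arm the standard error of the difference in shares is √(2 × 0.35 × 0.65/80) = 0.075, so the 95% chance limit is 1.96 × 0.075 = 14.8 points. The shift is 0.148 × 33 = 4.9 points.

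**The case against.** **The protocol does not show that baseline ALT is prognostic.** A reader might infer from section 2.7 that it does. The passages concern rises during treatment, which are post-baseline, and two patients cleared virus without any rise. This objection stands: the ALT odds ratios above are assumptions.

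**Covariates can be set in the statistical analysis plan.** A reader might infer that no planned analysis can adjust for these factors. The documents do not support that, because the analysis plan is not shown, ALT is in a determinations table with a baseline column, and nothing bars its use. What stands is narrower. The protocol itself fixes a list and a selection rule, and both are badly chosen, so this is not merely a detail left for later.

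**Viral load may already carry the HBeAg effect.** Section 2.7 attributes the poorer HBeAg-positive result to higher baseline viral load, which is listed. This reduces the likely residual bias, but the screening rule does not ensure that viral load stays in the model.

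**One more logistic term does not touch a 20-point criterion.** A logistic model yields an odds ratio, and the gain in precision is small: the assumed ALT effects explain only 1.4–9.8% of variance. This is correct and shapes the fix, which needs a standardised risk difference.

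**The larger shifts are exaggerated.** Under random allocation, 0.5 SD is implausible, and at one standard error (0.158 SD) the shifts are about half those in the 0.3 SD column. This also stands.

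**Conclusion.** The point holds in limited form. The control list omits baseline ALT and baseline HBeAg status, the one multivariable efficacy model described draws on that list after screening, and nothing described balances the arms on either factor. HBeAg status is the better documented omission, since the protocol reports different viral clearance by it; baseline ALT is plausible but unproven on this text.

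On assumed odds ratios of 1.3–2.0 per SD, a 0.3 SD imbalance in log ALT shifts the HBV DNA difference by about 2–5 points. The HBeAg illustration gives a similar figure, about 5 points at the chance limit, and rests on 20 earlier patients and on reading the 50% as 10 of 20. Neither is an estimate of actual bias. Shifts of this size matter only if the result lies near the 20-point criterion, so this is an inexpensive improvement that should be made rather than a flaw that invalidates the comparison.

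**What to change.** - In section 7, Control variables, add baseline ALT (log scale) and baseline HBeAg status.
- In section 10, pre-specify a model of undetectable HBV DNA at one year with treatment group, log ALT, HBeAg status and initial viral load, all entered without univariate screening. State explicitly that it applies to HBV DNA.
- From that model, report the standardised risk difference with its confidence interval beside the unadjusted difference, so that the adjusted result can be read against the 20-point criterion.
- Show baseline ALT and HBeAg status by arm in the baseline table.

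The cost is a few degrees of freedom and a few lines of text. Both values are already needed to establish eligibility, so no new measurement is required.

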#### **Variables used to measure the effects and periodicity of the determinations**

The clinical parameters will be evaluated by the investigator taking into account the information that the patient offers and the physical examination. The laboratory parameters will be measured by the usual methods of clinical laboratory. The information will be registered in the case report forms.

In the following table the evaluation parameters and their frequency are included.

#### **Evaluation criteria regarding safety**

All AE that appear during the study will be recorded in the Case Report Form of each individual.

All medical incidents that occur in the first hour after each administration of the vaccine, causally related or not with the vaccination will be recorded.

The rest of the observations will be evaluated in the follow up visits every 14 days.

The observation includes medical questionnaire of the patient, inspection of the injection site, axillary's temperature, and registration of all symptoms and signs referred by the patient. Explanation of how to act in case of abandonment or exit in the trial

The patients that abandon the trial will always be evaluated, except if the investigator loses contact with him. The information will be registered in the Case Report Form (CRF), including the cause of exit.

Quality control of the evaluation procedure

The clinical and laboratory evaluations will be preserved, in order to be examined by external quality controllers.

All primary data should be collected and conserved during the study.

The frequency of specific determinations as well as the type of determination per specific date according to the protocol are presented below: (Grey boxes: Determinations will not be performed).

| Test                    | Baseline
(not more than 2 months before starting treatment) | Week 12 | Week 24
EOT-V | Week 36 | Week 48
EOT-I | Week 72 | Week 96 | Reference Values
(M: male, F: female) |
|-------------------------|----------------------------------------------------------------|---------|------------------|---------|------------------|---------|---------|------------------------------------------|
| Hemoglobin              |                                                                |         |                  |         |                  |         |         | M: 12-17 g/dL
F: 11.5-15.5 g/dL       |
| Hematocrit (PCV)        |                                                                |         |                  |         |                  |         |         | 37-54%                                   |
| Leukocytes              |                                                                |         |                  |         |                  |         |         | 4-10 x 10  /L                |
| Neutrophils             |                                                                |         |                  |         |                  |         |         | 40-80%                                   |
| Lymphocytes             |                                                                |         |                  |         |                  |         |         | 20-40%                                   |
| Eosinophils             |                                                                |         |                  |         |                  |         |         | 1-6%                                     |
| Basophils               |                                                                |         |                  |         |                  |         |         | Up to 1%                                 |
| Plateles                |                                                                |         |                  |         |                  |         |         | 150-400 x 10  /L             |
| Random Blood Sugar      |                                                                |         |                  |         |                  |         |         | 3.9 – 7.7 mmol/L                         |
| S. Creatinine           |                                                                |         |                  |         |                  |         |         | M: 60-130 µmol/L
F: 53-120 µmol/L     |
| S. Uric acid            |                                                                |         |                  |         |                  |         |         | M: 200-420 µmol/L
F: 140-340 µmol/L   |
| S. ALT                  |                                                                |         |                  |         |                  |         |         | Up to 42 U/L                             |
| S. AST                  |                                                                |         |                  |         |                  |         |         | Up to 37 U/L                             |
| S. Alkaline Phosphatase |                                                                |         |                  |         |                  |         |         | Up to 117 U/L                            |
| Gamma GT                |                                                                |         |                  |         |                  |         |         | M: ≤65 U/L
F: ≤45 U/L                 |
| S. Bilirubin            |                                                                |         |                  |         |                  |         |         | 0.6 mg/dl                                |
| HBV DNA                 |                                                                |         |                  |         |                  |         |         | Quantification                           |
| Anti-HCV                |                                                                |         |                  |         |                  |         |         | Negative                                 |
| Anti-HIV                |                                                                |         |                  |         |                  |         |         | Negative                                 |
| Anti-HBs                |                                                                |         |                  |         |                  |         |         | Up to 100,000 UI/L                       |
| HBsAg                   |                                                                |         |                  |         |                  |         |         | Positive                                 |
| HBeAg                   |                                                                |         |                  |         |                  |         |         | Positive / Negative                      |
| Anti-HBe                |                                                                |         |                  |         |                  |         |         | Positive / Negative                      |
| Anti-HBcAg IgM          |                                                                |         |                  |         |                  |         |         | Positive / Negative                      |
| USG of HBS              |                                                                |         |                  |         |                  |         |         |                                          |

In addition, ALT and AST determinations will be conducted after each administration of NASVAC in the corresponding group in order to further study or explore any potential damage.

